## Abstract

**Background:**

Difficulty falling asleep, staying asleep or poor-quality sleep (insomnia) is common in people with chronic obstructive pulmonary disease (COPD). Insomnia is related to greater mortality and morbidity, with four times the risk of mortality for sleep times below 300 min. However, insomnia medications are used with caution in COPD due to their potential adverse effects. While cognitive behavioral therapy for insomnia (CBT-I) is effective for people with primary insomnia and people with other chronic illnesses, the efficacy and mechanisms of action of such a therapy are yet unclear in people with both insomnia and COPD. The purpose of this study is to rigorously test the efficacy of two components of insomnia therapy – CBT-I and COPD education (COPD-ED) – in people with coexisting insomnia and COPD, and to identify mechanisms responsible for therapy outcomes. The rationale for the proposed study is that once the efficacy and mechanisms of CBT-I and COPD-ED are known, new and innovative approaches for insomnia coexisting with COPD can be developed to non-pharmacologically minimize insomnia and fatigue, thereby leading to longer, higher-quality and more productive lives for people with COPD, and reduced societal cost due to the effects of insomnia.

**Methods:**

We are conducting a randomized, controlled, parallel-group (*N* = 35 each group) comparison of CBT-I, COPD-ED and non-COPD, non-sleep health education Attention Control (AC) using a highly efficient four-group design. Arm 1 comprises 6 weekly sessions of CBT-I + AC; Arm 2 = 6 weekly sessions of COPD-ED + AC; Arm 3 = 6 weekly sessions of CBT-I + COPD-ED; and Arm 4 = 6 weekly sessions of AC. This design will allow completion of the following specific aims: (1) to determine the efficacy of individual treatment components, CBT-I and COPD-ED, on insomnia and fatigue, (2) to define the mechanistic contributors to the outcomes after CBT-I and COPD-ED.

**Discussion:**

The research is innovative because it represents a new and substantive departure from the usual insomnia therapy, namely by testing traditional CBT-I with education to enhance outcomes. The work proposed in aims 1 and 2 will provide systematic evidence of the efficacy and mechanisms of components of a novel approach to insomnia comorbid with COPD. Such results are highly likely to provide new approaches for preventive and therapeutic interventions for insomnia and fatigue in COPD.

**Trial registration:**

ClinicalTrials.gov Identifier: NCT01973647. Registered on 22 October 2013.

## Background

Approximately one fourth of adults worldwide have chronic obstructive pulmonary disease (COPD) [1], and half of them suffer from insomnia [2] (difficulty falling or staying asleep, or poor-quality sleep that interferes with daytime functioning [3]). Insomnia is related to greater mortality [4–6], with studies showing *four times the mortality risk* for sleep times below 300 min [5, 6]. Insomnia also produces morbidity – insomnia sufferers generate 75 % greater healthcare costs than individuals without insomnia [7]. Lost productivity from insomnia is estimated at US$63.2 billion annually in the US alone [8]. People with COPD experience debilitating fatigue and a gradual decline in function that are partly related to insomnia [9–11]. However, insomnia medications are used with caution in COPD due to potential respiratory effects, hypoxia and effects on cognition [12]. Common features of COPD, such as dyspnea, chronic inflammation and emotional arousal (anxiety and depression), also affect insomnia and can interfere with therapy outcomes. Cognitive behavioral therapy for insomnia (CBT-I), a therapy that provides guidance on changing unhelpful sleep-related beliefs and behavior, is a promising non-pharmacological treatment that has demonstrated effectiveness for insomnia, but the efficacy of components and mechanisms of action of CBT-I have not been thoroughly examined in people with insomnia coexisting with COPD.

Insomnia is prevalent in people with medical disorders, and therapy for insomnia might improve these medical disorders [13]. However, there are only a limited number of randomized, controlled studies in this area. Although evidence obtained from studies that included participants with cancer [14, 15], renal failure [16], chronic pain [17], osteoarthritis, [18] and COPD [19, 20] support the notion that CBT-I is effective in reducing insomnia when coexisting with chronic illness, no studies to date have examined CBT-I specifically for people with COPD. It is yet undetermined whether improving self-efficacy for the medical illness (i.e., COPD) mediates outcomes after CBT-I, but our preliminary data suggest that education on COPD topics, such as management of dyspnea and COPD exacerbations, may improve self-efficacy and reduce depression, indirectly reducing insomnia and fatigue [20].

Our long-term goal is to help develop safe and effective non-pharmacological interventions to minimize insomnia and its consequences in people with COPD. The purpose of this study is to systematically test the efficacy of two components of therapy for people with coexisting insomnia and COPD – CBT-I and COPD education (COPD-ED) – and to identify the mechanisms responsible for therapeutic outcomes. Our central hypothesis is that both CBT-I and COPD-ED will have positive, lasting effects on objectively and subjectively measured insomnia and fatigue. This hypothesis is consistent with preliminary data from our pilot study [20] comparing CBT-I and COPD-ED in people with insomnia coexisting with COPD. The pilot study results demonstrated feasibility of the two components and provided preliminary evidence of positive effects on outcomes, which differed in men and women. Given the prevalence of insomnia and its consequences, it is important not only to identify the most effective approach to minimize insomnia for those with COPD but also to identify the mechanisms responsible for the outcomes, as not all patients will benefit from CBT-I. The rationale for this study is that once the efficacy and mechanisms of CBT-I and COPD-ED are known, new and innovatively tailored interventions can be developed to non-pharmacologically minimize insomnia and fatigue, thereby leading to longer, higher-quality and more productive lives for people with COPD, and reduced societal cost due to the effects of insomnia. The clinical gains could be, unlike those of pharmacotherapy, sustained following treatment discontinuation. We are testing our central hypothesis by completing a randomized, parallel-group, 2 × 2 factorial design which results in four groups (*N* = 35 each group): CBT-I, COPD-ED, both CBT-I and COPD-ED, and neither [21, 22].

Results from previous studies of predictors of positive outcomes of CBT-I suggest that mechanisms include changes in sleep-related beliefs, sleep habits, emotional arousal and self-efficacy for sleep [23]. Thus, our contribution here is expected to be knowledge of the efficacy and mechanisms of the components of a novel insomnia therapy for people with COPD and a detailed understanding of which patients are most likely to benefit from the therapy. This contribution will be significant because it is a necessary step in the development of effective non-pharmacological therapies for insomnia coexisting with COPD. Once such advances in therapy for insomnia coexisting with COPD become available, results can be used to further develop and make available effective and efficient insomnia therapies for people with COPD. Components of therapy found to be most important for positive outcomes can be included in new, more efficient therapies. It is expected that what we learn will be equally applicable to the prevention of insomnia and fatigue in people with COPD, potentially leading to them having longer, higher-quality and more productive lives and to society having to burden lower costs related to insomnia in COPD.

We are testing components of a novel therapy (CBT-I and COPD-ED) in an understudied population using a highly efficient study design. Despite the established need for such a therapy for people with COPD, this group is understudied, perhaps because of challenges such as recruiting subjects with COPD and managing periodic exacerbations of COPD that could occur during treatment. Furthermore, people with insomnia coexisting with COPD are subject to exacerbations of their illness that predispose them to recurrent insomnia and may interfere with CBT-I outcomes. The research represents a new and substantive departure from the usual insomnia therapy, specifically by combining traditional CBT-I with disease-specific education (COPD-ED) to enhance self-efficacy for the management of COPD. Enhancing self-efficacy for COPD is likely to reduce insomnia and fatigue by attenuating the anxiety and depressed mood associated with the disease.

### Aim 1

To determine the efficacy of individual treatment components, CBT-I and COPD-ED, on insomnia and fatigue. Our hypothesis is that both components will decrease insomnia and fatigue at the end of the six-session treatment period, and that these differential effects will be sustained for at least 3 months post treatment.

### Aim 2

To define the mechanistic contributors to the outcomes after CBT-I and COPD-ED. Our hypothesis is that CBT-I and COPD-ED components impact insomnia and fatigue through complementary mechanisms. Positive changes in beliefs about sleep, sleep habits, self-efficacy for management of COPD (SEC) and sleep (SES), and reduced emotional arousal (EA) will mediate the improving conditions in insomnia and fatigue and that gender, inflammation and functional status will moderate the outcomes.

## Methods: participants, interventions and outcomes

### Conceptual framework

The conceptual framework (Fig. 1) for this proposal has its foundations in social learning theory [24] and cognitive behavioral theory [25], which emphasize the interplay of cognitive, behavioral and environmental factors. According to these theories, in order to participate in behavioral change, persons must possess the knowledge, skills and confidence necessary to self-regulate behavior and have a firm belief in their ability to initiate change and change these behaviors. All individuals have personal traits that influence their predisposition to insomnia by impacting the degree to which they are physiologically, emotionally or cognitively hyper-aroused and unable to sleep. In our conceptual framework, COPD-related factors contributing to the illness burden can be predisposing or precipitating factors for insomnia. Cognitive factors, such as dysfunctional beliefs about sleep, emotional arousal such as anxiety and depression, and low self-efficacy for sleep and self-management of COPD, can also contribute [26]. For people with COPD, insomnia is likely to increase symptom burden and affect the ability to function in daily life. The components of our intervention target the factors that contribute to insomnia and promote its chronicity [27]. The efficacy of CBT-I on outcomes in COPD is unclear but must be clarified to develop effective non-pharmacological interventions specifically for insomnia coexisting with COPD. Future CBT-I programs will benefit from this information, which will provide guidance on potential components to include in CBT-I.

**Fig. 1 Fig1:**
[figure not shown]
Conceptual model

### Trial design

We are conducting a 2 × 2 factorial randomized trial where participants are randomized into four groups created by crossing the two factors, CBT-I versus Attention Control (AC)1 and COPD-ED versus AC2 (*N* = 35 each group). Arm 1 is comprised of 6 weekly sessions of CBT-I + AC1; Arm 2 = 6 weekly sessions of COPD-ED + AC2; Arm 3 = 6 weekly sessions of CBT-I + COPD-ED; and Arm 4 = 6 weekly sessions of AC1 + AC2. Each session is approximately 75 min in length. There is follow-up at 3 months post intervention. Dependent variables include objectively and subjectively measured insomnia and fatigue, measured three times: at baseline (pretest, T1), immediately post intervention (posttest, T2), and at 3 months (follow-up, T3) to provide data on the long-term effects of the interventions. In addition to these times, mediator variables are measured after the fourth session to improve our ability to test a causal mediating effect.

#### Setting and sample

The setting for the study is the University of Illinois at Chicago (UIC) College of Nursing Center for Narcolepsy, Sleep and Health Research (CNSHR) and Edward Hines, Jr. Veterans Administration (VA) Medical Center. Institutional Review Board approval was obtained from both institutions and all subjects sign a written informed consent. A total of 166 subjects with mild to very severe COPD as defined by the GOLD standards will be randomly assigned to one of the four groups. Subjects will be stratified by disease severity and gender.

*Inclusion criteria* include: (1) mild to very severe COPD. Severity of COPD is defined according to the new GOLD standards [28], (2) age 45 years or older with no other major health problems, (3) clinical stability at the time of enrollment into the study without major exacerbation of COPD within the previous 2 months, (4) difficulty initiating or maintaining sleep, waking up too early or poor-quality sleep (insomnia) [3].

*Exclusion criteria* include: (1) evidence of restrictive lung disease or asthma, (2) pulse oximetry (oxygen saturation: SaO_2_) reading of less than 90 % at rest or less than 85 % at night for more than 5 min, (3) evidence of a major sleep disorder other than insomnia, (4) hypnotic use, (5) acute respiratory infection within the previous 2 months, (6) the presence of a potentially debilitating disease such as cancer, congestive heart failure, kidney disease, liver failure or cirrhosis; evidence of alcohol or drug abuse, musculoskeletal or degenerative nerve disease. (7) a self-reported current diagnosis of major depression or psychiatric disease or a Hospital Anxiety and Depression Scale (HADS) depression score of >11, (8) currently participating in pulmonary rehabilitation. Potential subjects are screened to ensure that they meet the inclusion criteria.

#### CBT-I, COPD-ED and AC interventions

For both groups, sessions consist of six weekly group sessions, 75 min in length, administered in an individual or small-group (two to four persons) setting. The sessions are provided by clinicians trained in CBT-I, COPD-ED and the AC health education. Although the intervention period is relatively brief, we expect that some subjects will miss sessions. Subjects are allowed to make up classes within 2 weeks, for up to two sessions. The CBT-I component is based on Morin [29] and Perlis [30] and includes a program of stimulus control therapy (SCT), sleep-restriction therapy, sleep hygiene, cognitive therapy and relaxation therapy. The COPD education component (COPD-ED) is modeled after the COPD education program used in a previous study. Briefly, topics include how the lungs work; overview of COPD; managing COPD, including techniques for managing dyspnea; discussion of COPD medications; preventing and coping with exacerbations, flu and colds; and preventing complications of COPD. Table 1 summarizes the components of the CBT-I and COPD-ED interventions. These topics are presented using brief PowerPoint presentations, discussion and handouts. The CBT-I + COPD-ED intervention is a combination of CBT-I and COPD education. Each intervention session contains a CBT-I segment and a COPD education segment, for a total of approximately 75 min (Table 1). Topics include managing insomnia and COPD using strategies known to be effective. The AC intervention is comprised of six sessions of social support and general health education. Education excludes sleep and COPD topics and includes information about topics such as cholesterol, blood pressure, color perception, vitamins and memory.

**Table 1 Tab1:** CBT-I and COPD-ED topics

Session	CBT-I	COPD-ED
1	Orientation, “Background on sleep”	Orientation, “How the lungs work”
2	What is insomnia?	What is COPD?
3	Managing insomnia	Managing COPD
4	Managing insomnia, medications	Managing COPD, medications
5	Managing insomnia, techniques	Managing COPD, exacerbations, flu, colds
6	Insomnia relapse prevention	Preventing complications of COPD

*CBT-I* cognitive behavioral therapy for insomnia, *COPD-ED COPD* education, *COPD* chronic obstructive pulmonary disease

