#### Power analysis

Power analysis for aim 1 is based on main effect differences at the end of the intervention. We estimated the per cell sample size assuming a moderate effect size (Cohen’s *d* = 0.5), alpha = 0.05, and power = 0.80 using the fpower SAS macro available at http://www.datavis.ca/sasmac/fpower.html. Based on combined data from our pilot study measures, the minimum detectable difference (MDD) for the treatment main effects will be clinically meaningful. For example, we will be able to detect a 2.3-point difference in insomnia severity between those receiving COPD-ED versus those not, averaged across the other treatment conditions. The MDD for other outcomes includes Actiwatch® sleep efficiency = 6.72, CRQ-F = 0.51, and the Profile of Moods States Fatigue subscale (POMS-F) = 2.76. Between-group effect size estimates from our pilot study ranged from 0.35 for sleep efficiency to 1.03 for insomnia severity, comparing the proposed treatment components. Path models using 7–14 parameters can be estimated according to the sample size convention of 10 to 20 cases per parameter [61], thus, our simple path models can be estimated. We further conservatively estimate an attrition rate of 15 % by the end of the study. Therefore, we will enroll a total of 166 and retain 140 (35 per group) subjects in the proposed study.

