### Statistical analysis

#### Test of specific hypotheses

Descriptive statistics (means, standard deviation, frequency) and plots are used to screen the data prior to our main analyses. Necessary transformation and imputations are conducted based on the raw data distribution. Baseline adjustment for covariates (e.g., age, COPD severity (PFT), and gender) will be incorporated into the main effect analyses to reduce error variance and improve statistical power [69]. Data analyses is performed using SAS 9.3 statistical software (SAS Inc., Cary, NC, USA) and Mplus 6.0 (Muthén & Muthén, Los Angeles, CA, USA). All tests will be two-sided and an error rate of *α* <0.05 will be considered statistically significant. The test of each specific aim is described below, and all statistical analysis will employ an intent-to-treat approach. A fully specified statistical analysis plan will be written before unmasking.

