Aim 1: to determine the efficacy of individual treatment components, CBT-I and COPD-ED, on insomnia and fatigue. In this 2 × 2 design, participants are randomized into four groups created by crossing the two factors, CBT-I versus AC1 and COPD-ED versus AC2 (see Table 3). We hypothesize that both components will improve insomnia and decrease fatigue following the six-session program, and that participants will maintain these gains at 3 months post intervention. Our factorial design permits the test of an interaction between the two treatment components, and we will assess for the presence of a strong interaction effect. However, we do not anticipate a strong synergy of the treatments since our pilot work showed that both had within-group improvement, and the hypothesized mechanisms for change differ. If the interaction is negligible, we will proceed with the interpretation of averaged main effects as shown in Table 3. The statistical tests for both components will be more robust than tests against a simple control condition because they are averaged across the levels of the other treatment. That is, the effect of each component will be tested controlling for the effect of the other. This is an efficient design because all subjects will be used to test both components. Finally, it may be more acceptable to participants since all receive supportive contact and only one out of four conditions does not receive a component hypothesized as an active treatment for insomnia in COPD patients. We will employ mixed-effects models using insomnia and fatigue as time-varying dependent variables and treatment groups as fixed effects. Demographic and clinical characteristics will be entered as time-invariant covariates if baseline group differences are observed despite randomization. Individuals’ baseline sleep measures and change over time (i.e., intercept and slope) will be modeled as random effects. The null hypothesis will be rejected if a significant treatment × time interaction is observed. For example, a significant CBT-I × time effect in the hypothesized direction would mean that participants receiving CBT-I improved more than those who did not, averaged across the other conditions. The mixed models will be run using PROC MIXED SAS 9.3 (SAS Inc., Cary, NC, USA) and estimated by residual maximum likelihood (REML). Covariance pattern structures (compound symmetry and unstructured) will also be examined, and models will be compared using likelihood ratio tests or Akaike’s Information Criteria (AIC) which is a function of the log likelihood and can be compared across models.

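### Sessions may be given in small groups within an arm, but the Aim 1 model and the power calculation make no allowance for correlation within those groups

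*Protocol article*

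**What the plan says.** Under CBT-I, COPD-ED and AC interventions, the protocol article describes six weekly sessions, "administered in an individual or small-group (two to four persons) setting". It does not say how many participants receive each format. The Trial design section gives each arm its own combination of content.

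For Aim 1, under Test of specific hypotheses, the article states: "We will employ mixed-effects models using insomnia and fatigue as time-varying dependent variables and treatment groups as fixed effects". The treatment groups in that sentence are the study arms, not the session groups. The random effects named are the individual's baseline level and change over time. Compound symmetry and unstructured patterns are to be examined as covariance structures. All of these describe repeated measures within one person.

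Under Power analysis: "Power analysis for aim 1 is based on main effect differences at the end of the intervention". The inputs are a Cohen's d of 0.5, "alpha = 0.05, and power = 0.80 using the fpower SAS macro", and 15% attrition, leading to the statement that "we will enroll a total of 166 and retain 140 (35 per group) subjects in the proposed study". No ICC, session-group size or design effect appears there.

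**The concern.** Because each arm has its own content, a session group can in practice hold participants from one arm only. Its members share sessions and discussion, so their outcomes after treatment may be more alike than those of participants in different groups. Correlation of this kind, nested within arm, adds to the variance of an arm mean. A participant-level intercept and slope cannot absorb it, because it acts between people and not within a person.

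If it is left out, the reported standard errors for the CBT-I and the COPD-ED effects are too small, confidence intervals are too narrow, and the tests reject too often under the null. Both components are affected, since the delivery format is described in common for the interventions. Precision assumed at the planning stage may also be lost.

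**Working it through.** **Inputs from the protocol article.** d = 0.5, alpha = 0.05, power = 0.80 and 140 retained of 166 enrolled (Power analysis); two-sided tests (Test of specific hypotheses); main-effect comparison of 70 v 70 (Table 3); session groups of two to four, or individual delivery (CBT-I, COPD-ED and AC interventions).

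**Assumed.** An ICC of 0.01 to 0.10, and first that everyone is treated in groups of one size m. The article supplies neither.

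**Step 1: the plan's own figure.** For a main effect with independent participants, power comes from a noncentral t with N − 4 degrees of freedom and noncentrality d·√(N/4).
- 80% power at d = 0.5 needs 128 in total (32 per cell; power 0.801).
- With N = 140 the noncentrality is 0.5·√35 = 2.96 and power is 0.836 (0.841 by the normal approximation).
- Enrolment: 140/0.85 = 164.7, so 165 against the stated 166.

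The plan therefore retains 140 − 128 = 12 more participants than independence requires.

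**Step 2: clustering.** With design effect DE = 1 + (m − 1)·ICC:
- true standard error ÷ unadjusted standard error = √DE;
- type I error of the unadjusted test = 2·[1 − Φ(1.96/√DE)];
- power of a correctly sized test = noncentral t with noncentrality d·√(N/(4·DE)).

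Example with m = 3 and ICC = 0.05: DE = 1 + 2 × 0.05 = 1.10 and √DE = 1.049. Type I error is 2·[1 − Φ(1.869)] = 0.062. The noncentrality is 0.5·√(140/4.40) = 2.82, giving power 0.800.

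| m | ICC | DE | SE ratio | Type I error, unadjusted | Power, N = 140 |
|---|---|---|---|---|---|
| 2 | 0.01 | 1.01 | 1.005 | 0.0511 | 0.832 |
| 2 | 0.05 | 1.05 | 1.025 | 0.0558 | 0.818 |
| 2 | 0.10 | 1.10 | 1.049 | 0.0617 | 0.800 |
| 3 | 0.01 | 1.02 | 1.010 | 0.0523 | 0.828 |
| 3 | 0.05 | 1.10 | 1.049 | 0.0617 | 0.800 |
| 3 | 0.10 | 1.20 | 1.095 | 0.0736 | 0.765 |
| 4 | 0.01 | 1.03 | 1.015 | 0.0535 | 0.825 |
| 4 | 0.05 | 1.15 | 1.072 | 0.0676 | 0.782 |
| 4 | 0.10 | 1.30 | 1.140 | 0.0856 | 0.731 |

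A simulation of the unadjusted test (40,000 runs per setting, 36 per cell so that groups divide evenly) gave type I errors of 0.060 and 0.074 for m = 3, and 0.069 and 0.088 for m = 4, at ICC 0.05 and 0.10. These agree with the formula.

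**Step 3: where 0.80 fails.** Power at N = 140 equals 0.80 when DE is about 1.10. Solving (m − 1)·ICC = 0.10 gives an ICC of 0.10 for groups of two, 0.05 for groups of three and 0.033 for groups of four.

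**Step 4: mixed delivery.** If half are treated individually and half in threes, DE is approximately 1 + 0.5 × 2 × ICC, which is 1.05 at ICC 0.05 and 1.10 at ICC 0.10. Power is then 0.818 and 0.800, and type I error about 0.056 and 0.062.

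**The case against.** **The analysis plan.** The article promises a fully specified plan before unmasking, and that plan is not shown; it could add a session-group term. But the article does not leave the random effects open. It names them, and the covariance alternatives it lists are also within-person. The point is about the model as written, and it can still be corrected before unmasking.

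**Individual delivery.** Participants treated individually add no session-group clustering. If most are treated that way, the problem nearly disappears. This stands, and it is why the table is a bound for full group delivery.

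**The power claim.** A reader might infer that the stated power is optimistic. The figures do not support that in general: the article claims 0.80, the retained sample gives about 0.84 under independence, and the surplus absorbs a design effect of about 1.10. Nor does anything in the article support a more severe case, such as an ICC of 0.15 in groups of four with type I error near 0.10.

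**The planned test.** The calculations compare one time point, whereas Aim 1 tests treatment by time over three occasions. The end-of-intervention contrast is the one the article powers, so it is a fair basis for size, but the ICC of change could differ. Covariate adjustment, also planned, may recover some power. Clinician effects are not counted and could add to the correlation.

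**Group membership.** The article does not say that a group keeps one clinician, and up to two missed sessions may be made up. Membership is therefore not perfectly clean, which bears on how the group is defined. That groups hold one arm only is an inference from the arm-specific content.

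**Conclusion.** The point holds in a limited form. As written, the Aim 1 model ignores correlation among participants treated in the same session group, and its standard errors are too small whenever that correlation is positive. Over an assumed ICC of 0.01 to 0.10 with everyone in groups of two to four, the unadjusted standard error is about 0.5% to 12% too small (1/1.005 to 1/1.140) and type I error is about 0.051 to 0.086. Both are smaller when part of the sample is treated individually.

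The stated power of 0.80 survives up to a design effect of about 1.10. It falls short only with larger groups and a higher ICC: for example 0.78 at ICC 0.05 and 0.73 at ICC 0.10 with groups of four. The main consequence is a modest excess of false positives for both components. The size depends on two quantities that the article does not give, the ICC and the split of delivery format.

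**What to change.** - Record for each participant the session group first assigned. Make-up sessions attended elsewhere do not change it.
- In the Aim 1 model, add a random effect for session group within arm that applies to the post-baseline occasions only, since randomisation follows baseline testing. Treat individually treated participants as clusters of one, and use Kenward-Roger degrees of freedom.
- Report the estimated ICC and the numbers treated individually and in groups of each size.
- Use the same identifier for cluster-robust standard errors in the Aim 2 path models.
- State in the power section that 0.80 at d = 0.5 with 140 retained holds only up to a design effect of about 1.10.

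The cost is one identifier and one further random term, with no more participants. The attendance records already kept are a natural source, although the article does not say that they identify the session group, so this should be checked. Intervals will be slightly wider, and the session-group variance may be imprecisely estimated with clusters this small.
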